**Methods:**

AuToDeCRA-2 is a non-commercial, phase IIa, 5-arm, randomised, unblinded, single-centre study. It is designed to demonstrate and compare immunomodulation achieved by TolDC administered via three distinct routes: intra-nodal, intra-articular, intra-dermal and, in the case of intra-nodal administration, at 2 doses. Participants will be randomised to one of these four active intervention arms or standard care. Participants in intervention arms will receive a single dose of TolDC loaded with synthetic citrullinated peptides (TolDC_CitPep_) representing disease relevant autoantigens. Twenty Anti-Citrullinated Peptide Antibody (ACPA) positive, shared epitope positive Rheumatoid Arthritis patients with nil-to-moderate disease activity will be randomised in an allocation ratio of 1:1:1:1:1.

Participants will be followed up with immune state monitoring performed on peripheral blood samples at baseline, 1, 3 and 6 weeks and lymph node aspirates at baseline and 1 week, alongside clinical assessment performed throughout and additionally at 12 weeks.

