### Objectives {7}

AuToDeCRA-2 is designed to demonstrate and compare immunomodulation using synthetic citrullinated peptide-loaded TolDC (TolDC_CitPep_) administered via three distinct routes: intra-nodal, intra-articular, intra-dermal and in the case of intra-nodal administration, at a low and a high dose. The rationale for loading TolDC with citrullinated peptides is explained in section ‘Intervention description {11a}’.

Table 1 outlines the study objectives which will be achieved by comparing baseline data with follow-up data at 1, 3, 6 and 12 weeks.

**Table 1 Tab1:** Study objectives

Primary objectives	Secondary objectives	Exploratory objectives
• To seek signals of immune modulation when TolDC_CitPep_ are administered to participants with RA using immune state biomarkers performed on peripheral blood samples at baseline, 1, 3 and 6 week follow-up and participant lymph node aspirates at baseline and 1 week follow-up	• To seek signs of clinical efficacy when TolDC_CitPep_ are administered to participants with RA using ACR 20, 50 and 70, DAS-28, and components thereof at baseline and 1, 3, 6 and 12 week follow-up • To provide further evidence of TolDC_CitPep_ safety using reported adverse events (AEs) at baseline, 1, 3, 6, and 12 week follow-up • To provide further evidence of participant acceptability of TolDC_CitPep_ therapy for RA using a Participant Acceptability questionnaire at 12 week follow-up	• To link signals of immune modulation with signs of potential efficacy of TolDC_CitPep_ using potential associations between immune modulation measures and evidence of efficacy for the three different routes of TolDC_CitPep_ administration (and, in the case of intra-nodal injection, for the two doses administered) • To compare intra-nodal (low and high dose), intra-dermal and intra-articular injection with regards to primary and secondary objectives, and feasibility

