#### Exploratory Endpoint/Outcome Measures

Exploratory outcome measures for the study are:Enumeration and phenotypic analysis of autoreactive T cells by major histocompatibility complex class II tetramer stainingSingle cell RNA sequencing of peripheral blood T cells and lymph node aspiratesPotential associations between immune modulation (as defined by primary outcome measures) and evidence of efficacy (as defined by secondary outcome measures) for (1) the different routes of TolDC_CitPep_ administration (intra-articular, intra-dermal and intra-nodal) and (2) the different doses of TolDC_CitPep_ administered via the intra-nodal route (10^5^ and 10^7^)Comparison of (1) the different routes of TolDC_CitPep_ administration (intra-articular, intra-dermal and intra-nodal) and (2) the different doses of TolDC_CitPep_ administered via the intra-nodal route (10^5^ and 10^7^), for evidence of immune modulation and potential efficacy

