### Sample size {14}

There are no relevant background data available to power this study, which is exploratory and not powered for statistical significance. The sample size of 20 is based upon expected feasible recruitment into a complex experimental medicine protocol, based on prior experience from AuToDeCRA.

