### Plans for collection, laboratory evaluation and storage of biological specimens for genetic or molecular analysis in this trial/future use {33}

NHS laboratory and tissue typing bloods

Participants will provide NHS laboratory blood samples, which will be analysed in local Trust laboratories and then discarded. These will be collected and tested as per Table 2 below.

**Table 2 Tab2:** NHS laboratory blood samples

Blood set	Tests to be performed	Time points collected	Participants
Set 1	• Cyclic Citrullinated Peptide Antibody (Anti-CCP) • Rheumatoid factor (RhF) • Full blood count (FBC) • Erythrocyte sedimentation rate (ESR) • Coagulation Screen (with derived Fibrinogen) • International normalised ratio (INR) • Urea and electrolytes (U + E) • Magnesium (Mg) • Adjusted calcium • Liver function test (LFT) • C-reactive protein (CRP) • Human immunodeficiency virus (HIV) • Hepatitis B + C • Human T cell Leukaemia Virus (HTLV) 1 + 2 • Syphilis • Cytomegalovirus (CMV) • HLA DRB1 tissue type (except where tissue type is already known) • Follicle-stimulating hormone (FSH) *	Screening	All * FSH can be considered to prove post menopausal state in women < 50 years who have been amenorrhoeic for 12 months and would prefer testing to using contraception for the duration of the study on discussion with the investigator
Set 1B	• HIV • Hepatitis B + C • HTLV 1 + 2 • Syphilis • CMV	Secondary screening visit	Those screened > 38 days before scheduled baseline visit
Set 2	• FBC • U&E • LFT • Phosphate • Mg • Adjusted calcium • Group + Save • HIV • Hepatitis B + C • HTLV 1 + 2 • Syphilis	Leukapheresis visit	All, except participants randomised to Group 5 (control group)
Set 3	• FBC • U&E • LFT • CRP • ESR	Baseline, follow-up visits 1, 2 and 3	All
Set 4	• FBC • U&E • LFT • CRP • ESR • RhF • ACPA	Follow-up visit 4	All
Set 5	• FBC • U&E • LFT • CRP • ESR • Any additional test at the discretion of the investigator	Flare visit	Those completing a flare visit

Peripheral blood research biomarkers

Research blood samples will be obtained at baseline and weeks 1, 3 and 6. This will involve the collection at each visit of 108 ml of blood in a combination of EDTA and serum separator tubes. Some of this sample will be studied immediately within the research laboratory and the remainder processed and cryopreserved for analysis following study completion.

Lymph node aspirate samples

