## Statistical methods

### Statistical methods for primary and secondary outcomes {20a}

AuToDeCRA-2 is not powered for formal statistical significance. Nonetheless, a statistical analysis plan will be developed during the study.

The analysis population will include all subjects who have received their allocated intervention. For AE reporting, the analysis population will be all individuals who provide consent, whether or not they subsequently receive TolDC_CitPep_.

Demographic characteristics, medical history and clinical characteristics collected at screening will be summarised descriptively and tabulated. For categorical variables, the frequency and percentage in each group will be reported. For continuous variables the mean, standard deviation and/or median and interquartile range will be reported.

Within each arm (*n* = 4), we will assess whether there are any consistent trends in the parameters being measured, both for primary and secondary outcomes, and we will compare each of the 4 intervention arms against the control group and each other for primary and secondary outcomes.

Summary statistics capturing differences in immune biomarkers (expressed as percentages, stimulation indices, titres, etc.) and clinical outcomes (descriptive and numeric) will be tabulated and presented graphically. Longitudinal analysis will be performed to compare samples following TolDC_CitPep_ administration at baseline. Given the low participant number in each group (4), no formal statistical testing will be performed other than to explore analysis methods, identify prospective transformations of the data, identify key prospective time points and obtain estimates of the variability in both primary and secondary measures to inform the design of a future efficacy study. Estimates of variability will be based on a mixed effects model including participant, route of administration and sampling time point.

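### The variability model uses route of administration, not the five randomised arms, so it merges the two intra-nodal doses, gives the control arm no level, and counts any dose difference as variance

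*Protocol article*

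**What the plan says.** The section on statistical methods for primary and secondary outcomes {20a} rules out formal testing except for a few exploratory purposes. One of these is to "obtain estimates of the variability in both primary and secondary measures to inform the design of a future efficacy study". The next sentence gives the method: "Estimates of variability will be based on a mixed effects model including participant, route of administration and sampling time point". This is the only model that the article names.

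Elsewhere the design is built on arms:
- Participants "will be randomised in an allocation ratio of 1:1:1:1:1", which is 20 people, 4 per arm.
- The objectives {7} list three routes and add, "in the case of intra-nodal administration, at a low and a high dose".
- The sequence generation section {16a} lists five groups: intra-nodal 10^5, intra-nodal 10^7, intra-articular 10^7, intra-dermal 10^7, and standard care with nothing administered.
- The exploratory outcomes list the comparison of routes and, as a separate item, the comparison of "the different doses of TolDC_CitPep_ administered via the intra-nodal route".
- Section {20a} also says "we will compare each of the 4 intervention arms against the control group and each other for primary and secondary outcomes".

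On sampling, "Research blood samples will be obtained at baseline and weeks 1, 3 and 6", so the blood biomarkers have one pre-dose and three post-dose samples per participant. A statistical analysis plan is announced but not shown.

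**The concern.** Route has three levels and the randomisation has five. A model with route as its treatment factor treats the eight intra-nodal participants as one group, although their doses differ 100-fold and the protocol treats dose as a question of its own. It also has no defined place for the four controls. They either become an unstated fourth level or drop out of the fit.

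Any real difference between the two doses then has nowhere to go but the variance components. Part of it appears as extra spread between participants and part as extra within-participant scatter, because the difference exists only after day 0. These components are what the next trial's sample size would be built on. If dose matters, the planning variances are too large, and by more the more dose matters.

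**Working it through.** **No figure to reproduce.** The sample size section {14} says "There are no relevant background data available to power this study, which is exploratory and not powered for statistical significance", and no SD or effect size is given. What can be checked is how much an omitted dose effect adds to the variance estimates.

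**Inputs from the protocol.** 5 arms x 4 participants x 4 blood samples (day 0, weeks 1, 3, 6) = 80 observations.

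**Assumptions.** Complete data; controls coded as a fourth route level; effects constant after dosing; between-participant SD 1 and within-participant SD 0.5 (variances 1 and 0.25). Let D be the post-dose difference between the two intra-nodal doses.

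**Step 1: within-participant variance, route x time included, doses merged.**
- Each intra-nodal arm lies D/2 from the merged mean after dosing. The before/after contrast has squared length 3 x (1/4)^2 + (3/4)^2 = 0.75 per participant.
- Unexplained sum of squares = 8 x (D/2)^2 x 0.75 = 1.5 D^2.
- Residual df = 80 - 20 - 3 - 9 = 48, so the residual variance gains 1.5 D^2/48 = 0.03125 D^2.

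| D, in within-participant SDs | D | Within-participant variance | Inflation |
|---|---|---|---|
| 0 (doses act alike) | 0 | 0.250 | 0% |
| 1 | 0.5 | 0.258 | 3.1% |
| 2 | 1 | 0.281 | 12.5% |
| 4 | 2 | 0.375 | 50% |

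The D = 1 and 2 SD rows are the case where the low dose does nothing and the other active arms shift by that amount. The 2 and 4 SD rows also cover intra-nodal effects of 0 and 2 or 4 SDs, with the other active arms halfway.

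**Step 2: between-participant variance, same model.**
- Participant means differ by 0.75 D between the doses, which adds 8 x (0.375 D)^2 / 16 = 0.0703 D^2 to the variance of participant means (16 df).
- The component is that variance less a quarter of the residual. For D = 1: 1 + 0.0625 + 0.0703 - 0.0703 = 1.06. For D = 2: 1 + 0.0625 + 0.2812 - 0.0938 = 1.25.

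**Step 3: what a future sample size would see.** If it is based on change scores, it scales with the within-participant variance, so the table applies directly. If it is based on single post-dose values, it scales with the total variance (true value 1.25): (1.016 + 0.258)/1.25 = 1.02 for D = 0.5, (1.0625 + 0.281)/1.25 = 1.075 for D = 1, and (1.25 + 0.375)/1.25 = 1.30 for D = 2.

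**Step 4: if no interaction is fitted.**
- The unexplained sum of squares becomes 4 x 0.75 x (sum over arms of squared deviations from the mean effect), on 80 - 20 - 3 = 57 df.
- For a common effect d in all four active arms that sum is 4 x (0.2d)^2 + (0.8d)^2 = 0.8 d^2, so the gain is 2.4 d^2/57 = 0.0421 d^2. With d of 1 or 2 within-participant SDs, the inflation is 4.2% or 16.8%, with no dose difference at all.
- If the low dose does nothing and the other active arms shift by 1 or 2 SDs, the total under this reading is 6% or 25%. With intra-nodal effects of 0 and 2 or 4 SDs and the other active arms halfway, it is 15% or 59%.

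**Step 5: five-level arm with arm x time.** The expected residual variance is 0.25 and the between-participant variance 1 in every scenario. Residual df = 80 - 20 - 3 - 12 = 45, and between-participant df = 15.

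**Step 6: sampling error for comparison.** On 57 df a 95% interval for a variance runs from about 0.71 to 1.50 times the estimate. On 15 df it runs from about 0.55 to 2.40 times (0.74 to 1.55 for the SD).

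**The case against.** The strongest reply has four parts.

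1. **The sentence lists factors and is not a formula.** A reader might infer an additive model with no arm-by-time term. The text does not say that. Interactions, coding and covariance structure are normal content of an analysis plan, and that plan is not shown. This stands, so the main figures above allow route x time, and the no-interaction figures are conditional. It does not rescue the factor itself: route is named, and adding route x time still leaves the two doses merged.

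2. **The model has a limited job.** A reader might infer that the trial cannot show its dose or treatment contrasts. That is not supported. Arm comparisons and within-arm trends are planned as tabulated and plotted summaries, and they do not rest on this model. This stands in full.

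3. **The larger inflations need large effects.** Differences of 2 to 4 within-participant SDs are assumptions, and nothing in the protocol says they are likely. At 1 SD the dose-related inflation is about 3%. This stands, and it is why a range is given.

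4. **The bias is small beside the sampling error and errs on the safe side.** Most of the inflations lie inside the intervals in Step 6, and the direction leads to a larger future trial, not an underpowered one. This stands as a reason for a lower grade. It is no reason to keep a factor that does not match the randomisation, since sampling error can be shown with an interval and this bias cannot.

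**Conclusion.** The point holds as a mismatch between the named model and the design. Route of administration neither separates the 10^5 and 10^7 intra-nodal arms nor gives the controls a level, while the same section promises comparisons among all five arms.

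The consequence is conditional: variance estimates are biased upward if the doses act differently, and not otherwise. Under the assumed SDs, and granting route x time, the within-participant inflation is about 3% to 12.5% for dose differences of 1 to 2 within-participant SDs, and reaches 50% at 4. A common treatment effect adds bias only if no interaction is fitted, which the documents leave open.

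Severity is minor to moderate. The study is exploratory and unpowered, no treatment comparison depends on this model, and the error is conservative for the next trial. The documents do not support calling it a defect that must be corrected before the trial can meet its aims.

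**What to change.** In section {20a}, or in the analysis plan still to be written, replace route of administration with the randomised arm at five levels, with standard care as one of them. State that the model contains participant (random), arm, sampling time point and arm x time. Report each variance component with a 95% confidence interval, so that users of the estimates see how imprecise they are at 4 participants per arm.

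The cost is one sentence and no new data. Residual df fall from 57 to 45 against a model without interaction, or from 48 to 45 against route x time. Between-participant df fall from 16 to 15.

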### Interim analyses {21b}

There is no planned formal interim analysis.

Participant flow through the study will be presented using a CONSORT diagram and updated monthly throughout recruitment as a guide.

### Methods for additional analyses (e.g. subgroup analyses) {20b}

We will assess for any potential relationships between primary immune outcomes and secondary clinical outcomes.

### Methods in analysis to handle protocol non-adherence and any statistical methods to handle missing data {20c}

An investigation of missing data will be undertaken to understand study withdrawals or missing appointments and whether these could be related to baseline factors or AEs. Where data are incomplete, existing data will be used for all analyses. There will be no attempt to impute missing data.

### Plans to give access to the full protocol, participant-level data and statistical code {31c}

The full protocol is available from the corresponding author on reasonable request.

Until publication of the study results, access to the full dataset will be limited to the Trial Management Group (TMG). Requests for data sharing with bona fide study teams outside of Newcastle University or NuTH will be considered by a Data Access Committee, with representation from the sponsor and Chief Investigator (CI). Data transfer will be subject to completion of a Data Sharing Agreement between Newcastle University and the end users.

There is no relevant statistical code to access.

## Oversight and monitoring

### Composition of the coordinating centre and trial steering committee {5d}

Study conduct at site will be led by the PI and supported by GCP trained and appropriately delegated research clinicians and nurses.

Newcastle Clinical Trials Unit (NCTU) manages the trial on behalf of the sponsor and will provide day-to-day support for the site and training, site initiation activities and routine monitoring activities.

The TMG will be responsible for the day-to-day running of the study and will consist of the CI, PI and delegated researchers, members of NCTU, sponsor and, as required, other members of the study team. The TMG will monitor all aspects of the conduct and progress of the study. TMG meetings will occur approximately monthly.

The Trial Steering Committee (TSC) will provide overall independent oversight of the study and will oversee study conduct and progress. The TSC will consist of an independent chair, together with at least two other independent members, a Patient and Public Involvement (PPI) representative and the CI. The TSC will meet approximately 6-monthly throughout the study.

### Composition of the data monitoring committee, its role and reporting structure {21a}

The Data Monitoring Committee (DMC) will consist of at least three independent members including an Independent Chair, an Independent Statistician and an Independent Clinician and will meet approximately 6-monthly throughout the study. The DMC will make recommendations to the TSC as to whether there are any ethical or safety issues that may necessitate changes to the study.

### Adverse event reporting and harms {22}

Participants will be asked to report AEs at every study visit and encouraged to contact the study team for any concerns between visits via 24-h telephone numbers.

All AEs occurring from point of consent to end of the last study-related assessment will be recorded in the AE eCRF and the participant’s medical records. All serious AEs will also be reported to sponsor and to the MHRA if applicable.

All SARs occurring from administration of TolDC_CitPep_ to last study-related assessment will be reported to sponsor and recorded in the eCRF and medical records.

The assessment of expectedness will be performed by the CI on behalf of the sponsor against the approved Reference Safety Information for the study.

Any suspected unexpected serious ARs will be reported to the MHRA and Research Ethics Committee (REC) by the sponsor.

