**Fig. 2 Fig2:**
[figure not shown]
Schedule of events

Screening will take place between day − 150 and day − 10. If screening takes place between day − 150 and day − 39 then a secondary screening visit will occur between day − 38 and day − 10. This is to ensure that the participant remains eligible and to allow for safety blood sampling in line with leukapheresis and TolDC production facility SOPs.

After screening and randomisation (and leukapheresis for those receiving TolDC_CitPep_), participants will attend for baseline (day 0) clinical and immunological assessments. All participants will provide a blood sample and an ultrasound-guided fine needle aspirate from inguinal lymph nodes. These blood and lymph node aspirate samples will contribute to the immunological endpoints described above. Participants in intervention arms will then receive TolDC_CitPep_ at the allocated dose and via the allocated administration route.

Participants will be followed up on four occasions at 1, 3, 6 and 12 weeks after the baseline visit. Clinical assessment and blood sampling will take place at each visit. At the week 1 follow-up visit, all participants will undergo a second lymph node ultrasound-guided fine needle aspirate.

If, during the follow-up period, a participant suffers deterioration in their arthritis symptoms, they will attend for a ‘flare visit’. A full clinical assessment will be performed and, if a flare of RA is diagnosed, the participant managed appropriately at the discretion of the investigator, according to standard care. If therapeutic intervention is required for the flare, final samples will be taken for immunological endpoints and the participant will exit the study.

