### Plans to promote participant retention and complete follow-up {18b}

The clinical research team will discuss appointment dates with participants to ensure suitability, provide appointment dates in advance and address any transport or accessibility needs. Dates and times can be provided in writing. Reminder phone calls will be made prior to leukapheresis and baseline appointments. Future appointment dates and times will be re-discussed at each appointment.

Participants can withdraw from the study at any time without providing a specific reason. Data collected to the point of withdrawal will be retained and utilised, although participants may request to have stored samples destroyed. Participants withdrawing will be asked for written permission to collect and use data from routine clinical follow-up for the period of their intended participation. Where the TolDC_CitPep_ have been administered, contact in line with a participant’s week 12 assessment will be attempted to check for adverse reactions (ARs).

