### Dissemination plans {31a}

A final report will be provided to the sponsor and REC within 1 year of the end of the study, defined as completion of all study related activities including completion of biomarker sample analysis for all participants.

Study results will be made publicly available on the ISRCTN trial registry within 1 year of the end of the study.

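### For participants who leave early, the rules on flare exit, post-withdrawal contact and AE/SAR windows do not fit together, so safety follow-up can stop well before week 12 and AE ascertainment among leavers can differ by arm

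*Protocol article*

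**What the plan says.** Three sections of the protocol article govern safety follow-up.

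- **Adverse event reporting and harms {22}** sets two windows with the same closing point. For adverse events: "All AEs occurring from point of consent to end of the last study-related assessment will be recorded in the AE eCRF". For serious adverse reactions: "All SARs occurring from administration of TolDC_CitPep_ to last study-related assessment will be reported to sponsor and recorded in the eCRF and medical records".
- **Participant timeline {13}** sets the schedule: "Participants will be followed up on four occasions at 1, 3, 6 and 12 weeks after the baseline visit". It also sets an early exit. If a flare needs therapeutic intervention, "final samples will be taken for immunological endpoints and the participant will exit the study". No later visit or contact is attached to that exit.
- **Plans to promote participant retention and complete follow-up {18b}** deals with withdrawal. Every withdrawing participant is asked for permission to use routine-care data over the intended participation period. Where TolDC were given, contact in line with the participant's "week 12 assessment will be attempted to check for adverse reactions (ARs").

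The number of reported AEs is a secondary outcome (Outcomes {12}). The AE population is everyone who consents, and each intervention arm is compared with control on secondary outcomes (Statistical methods {20a}). The study is unblinded {17a}.

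**The concern.** Each rule is clear by itself, but together they do not say how long safety data are collected from someone who leaves early. Both windows in section {22} close at the last study-related assessment. For a participant who exits because of a treated flare, that appears to be the flare visit. The one contact that could extend follow-up is described among the withdrawal rules, and a protocol-mandated exit is not clearly a withdrawal.

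Two things are at stake. First, Background and rationale {6a} takes the absence of flare after dosing in the earlier study as a sign that the cells kept their phenotype. Participants who flare are therefore of particular safety interest, yet they may have the shortest observation. Second, the contact is offered by exposure, with the arm known, and asks about reactions, while the outcome counts AEs. A call to a TolDC recipient can bring AEs to light that nobody asks a departed control about.

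**Working it through.** The plan gives no figure to reproduce. The check sets the rules side by side and then sizes the gap.

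**Inputs.** Follow-up of 12 weeks = 12 × 7 = 84 days (section {13}). Five arms of 4 = 20 participants, which agrees with Sample size {14}; 4 × 4 = 16 are allocated to TolDC and 4 to control. No rate of flare exit or withdrawal is given.

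**Step 1: what the rules give each kind of participant.**

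| Participant | Window closes | Contact after exit |
|---|---|---|
| Completer, any arm | Week 12 | Not needed |
| Withdrawn, TolDC given | Last visit, or week 12 if the contact counts as an assessment | Attempted at week 12, for ARs |
| Withdrawn, control | Last visit | None; routine data if permission is given |
| Treated-flare exit, TolDC given | Flare visit, or week 12 if the contact applies and counts | Not settled |
| Treated-flare exit, control | Flare visit | None stated |

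**Step 2: follow each reading through.**

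- If the week-12 contact does not apply to treated-flare exits, their window closes at the flare visit in all arms. The arms are then alike for these leavers, but follow-up is cut short.
- If the contact applies and counts as a study-related assessment, TolDC leavers have a window to week 12 while control leavers' window closed at exit.
- If the contact applies but does not count, a reaction learned of at the call that occurred after the last visit lies outside both windows in section {22}, and no recording rule is stated for it.

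No reading gives every early leaver active AE collection to week 12.

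**Step 3: size of the gap for one participant.** Days unobserved = 84 − 7 × exit week, assuming no later contact:

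- week 1: 84 − 7 = 77 days (77/84 = 92%)
- week 3: 84 − 21 = 63 days (75%)
- week 6: 84 − 42 = 42 days (50%)

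A flare visit can fall at any time; these weeks only illustrate the range.

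**Step 4: size for an arm.** Planned post-baseline exposure is 4 × 12 = 48 participant-weeks. One exit at week 1 removes 12 − 1 = 11 weeks, and 11/48 = 22.9%. This leaves out the time from consent to baseline, which the AE window also covers.

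**Step 5: size for the pooled TolDC group.** Assume that 0 to 4 of the 16 recipients exit early without later contact. Then 16 down to 12 have complete 12-week safety data. With no events of a given kind, the one-sided 95% upper bound is 1 − 0.05^(1/n): 17.1% for n = 16 and 22.1% for n = 12.

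**The case against.** The strongest case against the point has four parts.

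- **The flare itself is captured.** The flare visit includes a full clinical assessment, and Table 2 (Set 5) adds safety bloods. What may be lost is the time after flare treatment, when attribution to TolDC is confounded. This stands as far as attribution goes. It does not answer the AE count, which takes events whatever their cause.
- **A control cannot have a reaction to TolDC**, so checking only exposed leavers for reactions is a sensible targeted safety measure. That is fair as a safety measure. But the arms are compared on AEs, and an active call can raise the AE count on one side only.
- **The wording may already cover the case.** Nothing in section {18b} expressly excludes a protocol exit, and the week-12 contact might itself be the last study-related assessment. Both readings are possible, which is why the text needs settling.
- **The full protocol may say more.** An article condenses. Even so, the point rests on rules that the article states and that do not join up, not on detail left out.

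A reader might go further and infer that later serious reactions go unreported. The documents do not support that. Nothing bars later reporting. The sentence on suspected unexpected serious reactions has no closing date: "Any suspected unexpected serious ARs will be reported to the MHRA and Research Ethics Committee (REC) by the sponsor". Participants are also "encouraged to contact the study team for any concerns between visits via 24-h telephone numbers".

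A reader might also infer that follow-up is unequal by arm in general. It is not. The visit schedule, the AE window and the flare-exit rule are the same in all five arms, and the request for routine-care data goes to every withdrawing participant.

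**Conclusion.** The point holds for early leavers only. On the face of sections {13}, {18b} and {22}, a participant treated for a flare can leave safety follow-up with 92%, 75% or 50% of the 84 post-dose days unobserved (exit at week 1, 3 or 6). Whether the week-12 contact mends this is not settled. Among leavers, AE ascertainment can differ between TolDC and control arms.

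The figures assume that no contact takes place after exit. The number of early leavers is not given, so the total effect cannot be estimated; it is nil if nobody leaves early. With four participants per arm, one early exit is enough to disturb a raw AE count.

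Section {31a} defines the end of study as "completion of all study related activities including completion of biomarker sample analysis for all participants", and a reader might conclude that SAR reporting should run until then. The documents do not require it. That definition serves the timing of the final report and the registry results, it does not conflict with a participant-level safety window, and no section gives evidence of reactions after week 12.

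**What to change.** Reconcile the three sections:

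1. In section {22}, state that AEs (from consent) and SARs (from administration) are collected up to the planned week-12 date, whatever the date of exit. This also removes the doubt about what counts as the last study-related assessment.
2. In section {18b}, extend the attempted week-12 safety contact to every participant who leaves early for any reason, including a treated flare, in all five arms. Ask about all AEs, so that causality is not judged before the question is put.
3. In section {13}, refer to that contact where the treated-flare exit is described. The exit rule itself and the management of the flare are not at issue here.

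The cost is protocol wording and a few telephone calls by existing staff among 20 participants, with no added visit or sample. A few more events may be reported.
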